1.10. TEACHING INTENTION

APPLICATIVE INTENTION:

TYPE OF THESIS: Basic studies ____ Specialty __X__ Subspecialty ______

Master in Science ______ Ph. D. Program____

SCHOOL:

AUTHORIZATION:

EDUCATION ADDRESS:

**2. THEORETICAL ASPECTS**

2.1. BACKGROUND

Foetal death is one of the saddest and most devastating episodes in gynaecology, in which the mother suffers an intense emotional crisis, along with the father and the family. A long delay in labour can increase the risk of anxiety and psychological anguish related to long-term symptoms. Women with little social support are particularly vulnerable to anxiety and postpartum depression.1,2

After the diagnosis of intrauterine foetal death (IUFD), the majority of hospitalised patients opt to deliver the baby within 48 hours.3 However, in women whose pregnancies are not gynaecologically monitored, spontaneous labour within three weeks of foetal death can result in complications for new pregnancies as a consequence of intrauterine infection. The induction of labour in a pregnant woman with an unripe cervical opening can be associated with the failed induction of labour and, invariably, with birth by caesarean section. The pharmacological induction of labour is an obstetric procedure that artificially initiates uterine concentrations that lead to progressive dilation and cervical ripening prior to the administration of intravenous oxytocin.4 For the induction of IUFD, methods of cervical preparation include the vaginal administration of dinoprostone, gemeprost, misoprostol, oxytocin, and progesterone receptor antagonists.5,6 The main problems cited by women during the induction of labour are excessive uterine activity and ineffective labour, which, in association with a history of placenta praevia or uterine surgery, can cause an increase in the risk of uterine rupture.7,8

The therapeutic efficacy and safety of nitric oxide donor drugs has been reported, with isosorbide dinitrate used to induce cervical ripening during the first trimester of gestation.9 Organic nitrates are reductively metabolised to release nitric oxide (NO), which stimulates the activation of soluble guanylyl cyclase (GC). This activation leads to the conversion of GTP into cyclic guanosine monophosphate (cGMP), the second messenger involved in NO mediation.7 The increase in cGMP levels causes the relaxation of the smooth musculature.10-13 In addition, the organic nitrates participate in the endogenous NO production pathway in endothelial cells to maintain vascular tone.14-16 This mechanism has led to an interest in exploring the metabolic activity of NO and medical use of nitrovasodilatory drugs as potential inducers of cervical ripening.

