Nitric oxide (NO)-releasing drugs are a novel class of effective and safe agents for cervical ripening such as isosorbide dinitrate. Several chemical donors of NO are currently being used in various types of experimental and therapeutic studies.107 The NO donor, isosorbide mononitrate, is effective at inducing cervical ripening during the first trimester, prior to medical termination of pregnancy.108 Other NO donors, such as glyceryl trinitrate and sodium nitroprusside, administered during the first trimester, have fewer adverse effects than the prostaglandin analogue gemeprost.109 In contrast to the stimulatory actions of prostaglandins, activation of the NO system leads to myometrial relaxation and can be used to successfully treat intrapartum fetal distress caused by uterine hypertonus.110,111 A fall in maternal blood pressure, if severe, will compromise uteroplacental blood flow causing fetal hypoxia. Nevertheless, the risk of maternal hypotension is a potential problem when using an NO-releasing drug for cervical ripening due to its vasodilatory function. Induction of cervical ripening preoperative reduces morbidity in surgical termination of pregnancy, including those related to hemorrhage, incomplete emptying of the uterus, uterine perforation and cervical trauma.

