2.5. OBJECTIVE AND HYPOTHESIS

2.5.1. OBJECTIVE OF EXPERIMENT

The main objective of our study is to compare the efficacy and adverse effects of the intravaginal administration of isosorbide dinitrate in gel form followed by a high dose of oxytocin for the induction of labour after late foetal death with a commonly utilised combined regimen, misoprostol-oxytocin. Also, we will establish adverse events such as blood pressure, respiratory rate, and temperature, as well as nausea, headache, vomiting, diarrhea, fever, chills, abdominal pain and vaginal bleeding in women treated with misoprostol or isosorbide dinitrate.

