4.5. DATA COLLECTION

Data of the treatment will discarded, and only the study number will used to code the patient’s measurements. The type of treatment remained unknown to the participating women, and at the end of study period the results will analysed. All participants were given a vaginal exam by the same person, who was blinded to the treatment allocation. The medications were administered in the posterior fornix, and cervical activity was evaluated at baseline and every 3 hours to monitor any change based on the Bishop score.

If the cervical conditions did not change after the treatment application, participants will receive a new dose, without exceeding 4 doses, to facilitate cervical ripening. Once a Bishop score of over 7 will reached, oxytocin will infused in a balanced electrolyte solution beginning with an infusion rate of 2 mIU/min and doubling the dose every 15 minutes. The labour induction time from the first application of medication to the expulsion of the foetus will determined with a digital stopwatch. Each woman's vital signs will verified to determine that she is in stable condition and demonstrated haemodynamic stability as a requirement for the application of a new dose. During this time, the data and medical information will collected on paper and will later entered into a computational database. The participants will remain at rest during the evaluation of adverse effects, such as headache, abdominal pain, pelvic pain, lower back pain, nausea, dizziness, and vomiting. The lack of cervical activity after 4 doses of medication will considered treatment failure.

4.6. PILOT STUDY.

The purpose of conducting the pilot study will be examine the feasibility of an clinical approach study. Our pilot study can be used to evaluate the feasibility of recruitment, randomization, retention of patients and assessment procedures of the novel intervention. Ten women with ultrasonographic diagnosis of fetal death above 20 weeks gestation will be randomly selected to receive the pre-induction treatment based isosorbide dinitrate gel solution or misoprostol gel solution. The time interval between the application of pretreatment, the optimal relaxation of the cervix and conduction of labor will be determined in women in each experimental group. Also, clinical data obtained from these patients will serve to estimate the required sample size. Patients will have access to the best proven therapeutic method identiﬁed by the study.

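### The objective promises to compare vaginal bleeding between arms, but the data-collection list has no bleeding or retained-tissue item and describes no assessment after expulsion

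*Protocol*

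**What the plan says.** **What is promised.** Section 2.5.1 (Objective) lists the adverse events to be established: "nausea, headache, vomiting, diarrhea, fever, chills, abdominal pain and vaginal bleeding in women treated with misoprostol or isosorbide dinitrate". It gives no definition, quantity or time window for bleeding. Sections 2.2 and 2.4 also name vaginal bleeding among the unwanted effects of misoprostol and of prostaglandins generally.

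**What is collected.** The adverse-effect checklist in section 4.4 has seven symptoms, and section 4.5 repeats them: "such as headache, abdominal pain, pelvic pain, lower back pain, nausea, dizziness, and vomiting". Heart rate, respiratory rate, temperature and blood pressure are also recorded. Section 4.5 mentions vital signs in connection with re-dosing ("demonstrated haemodynamic stability as a requirement for the application of a new dose").

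**When observation ends.** The timing described runs up to expulsion: "The labour induction time from the first application of medication to the expulsion of the foetus will determined with a digital stopwatch".

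**What the mechanism is.** Section 2.1 gives the pharmacological rationale: "The increase in cGMP levels causes the relaxation of the smooth musculature". Section 2.4 applies it to the uterus: "activation of the NO system leads to myometrial relaxation".

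**How safety is judged.** Section 4.7 evaluates drug safety from the adverse-effect data, using relative risks with 95% confidence intervals.

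**The concern.** The objective names an outcome that the checklist gives no place to record. An analysis plan cannot repair this, because it cannot analyse a variable that was never collected.

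Bleeding also matters to this particular comparison. The protocol attributes it to the comparator's drug class, and it says the experimental drug's class relaxes the muscle of the uterus. Both arms therefore have a reason, on the protocol's own account, to be examined for it. If the form is completed as printed, the trial could report on clinical safety with nothing to say about bleeding, or about tissue left behind after expulsion.

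**Working it through.** **1. Objective against checklist.**

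| Event named in 2.5.1 | In the 4.4 / 4.5 lists? |
|---|---|
| Nausea, headache, vomiting, abdominal pain | Yes |
| Fever | Indirectly, through core temperature |
| Diarrhoea, chills | No |
| Vaginal bleeding | No |

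Blood loss, retained placenta or tissue, curettage, transfusion and extra uterotonic use appear in no outcome or data-collection section.

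**2. Timing.** Section 4.3 spaces administrations 3 hours apart, and section 4.5 allows at most four. A woman given all four at that spacing is dosed at 0, 3, 6 and 9 hours. If she meets the main outcome (expulsion within 15 hours, section 4.4), expulsion comes no more than 15 − 9 = 6 hours after her last dose. The protocol gives no duration of effect for the gel, so it does not settle whether any relaxation persists at that point.

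**3. The sample size.** Section 4.7 gives at least 30 per group from 97% v 67%, α = 0.05, power 80%.

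- Two-sided, uncorrected: [1.96·√(2·0.82·0.18) + 0.8416·√(0.97·0.03 + 0.67·0.33)]² / 0.30² = (1.065 + 0.421)² / 0.09 = 24.5.
- With continuity correction: (24.5/4)·[1 + √(1 + 4/(24.5·0.30))]² = 30.8, so 31.

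This is within one of the stated figure, so 30 per arm is used below. The point itself does not depend on this calculation.

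**4. What 30 per arm could show if the fields existed.** The protocol gives no event rates, so all rates here are assumptions.

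- Chance of at least one event among 30 women in one arm: 1 − 0.95³⁰ = 79% at a 5% rate; 1 − 0.90³⁰ = 96% at a 10% rate.
- Upper one-sided 95% limit if no event is seen in 30: 1 − 0.05^(1/30) = 9.5%.
- Power for a yes/no event, two-sided α = 0.05, uncorrected normal approximation:

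| Assumed rates | Power |
|---|---|
| 5% v 10% | 11% |
| 5% v 15% | 25% |
| 5% v 20% | 42% |
| 10% v 30% | 49% (exact enumeration of the chi-square test: 50%) |

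- Blood loss in mL: a two-sample t test has 80% power for a difference of 0.74 SD. The 95% CI for the mean difference has half-width 2.002·√(2/30) = 0.52 SD. No SD in mL is given in the protocol, so this cannot be turned into millilitres.

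**The case against.** **Bleeding is not absent from the protocol.** Section 2.5.1 lists it, and section 4.5 introduces its symptoms as examples, so a clinician might record bleeding anyway. That stands as a possibility. However, the 4.4 checklist has no such field, and nothing says when or how bleeding would be assessed. Whatever was captured would be unsystematic.

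**Post-expulsion atony is an inference.** A reader might conclude that the mechanism predicts a poorly contracting uterus. The documents do not support that strength. Section 2.4 presents myometrial relaxation as an advantage against hypertonus, section 2.3.1 describes nitric oxide's half-life as brief, no duration of effect is given for the gel, and oxytocin is infused in both arms once the Bishop score exceeds 7. Whether oxytocin continues after expulsion is not described. The harm is plausible, no more.

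**The nitrate's mechanism-based harms are not all missed.** The one that section 2.4 names is hypotension ("the risk of maternal hypotension is a potential problem when using an NO-releasing drug for cervical ripening due to its vasodilatory function"), and blood pressure is collected. So are headache, which section 2.5.2 expects from the nitrate, and dizziness.

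**The Justification's haemorrhage wording is not about this setting.** Section 2.4 refers to complications "including those related to hemorrhage, incomplete emptying of the uterus, uterine perforation and cervical trauma", which could be read as the protocol identifying third-stage risk. The sentence concerns morbidity in surgical termination that preoperative ripening is said to reduce. It cannot be used as an admission of risk after induced labour.

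**The direction of any bias is unknown.** One might infer that the omission flatters the nitrate. Sections 2.2 and 2.4 attribute bleeding to misoprostol and prostaglandins, so the omission could equally hide a harm of the comparator.

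**Power is low.** This is true, and it argues for estimates rather than tests. It does not argue for leaving the outcome unrecorded.

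**Conclusion.** The point holds in a limited form. A safety event promised in section 2.5.1 has no field in section 4.4, does not appear in section 4.5 and has no described assessment after expulsion, so section 4.7 cannot report it by arm if the checklist is followed as written. The related question of retained tissue is not recorded either. The omission could conceal a difference in either direction. It does not affect the main outcome, and haemodynamic effects, headache and dizziness are covered.

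The contradiction between sections rests on the text alone. The relevance of a post-expulsion window rests on an inference from the stated myometrial effect. The sizes rest on assumed event rates: at those rates at least one case among 30 women is likely (79% to 96% at 5% to 10%), but a comparison of yes/no events would have about 50% power at best over the range examined. This is a modest, cheap improvement to the safety data and does not invalidate the trial.

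**What to change.** Reconcile section 2.5.1 with sections 4.4 and 4.5. Add to the 4.4 checklist, over a stated window that extends past expulsion:

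- vaginal bleeding (yes/no);
- estimated blood loss (mL);
- extra uterotonic or transfusion given (yes/no);
- removal of retained placenta or tissue (yes/no).

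These are records of what happened; no change to treatment or clinical management is implied. In section 4.7, report blood loss as a mean difference with 95% CI and the yes/no events as counts by arm, labelled as descriptive safety estimates. The same pass should settle diarrhoea and chills, which section 2.5.1 also promises and the checklist also omits.

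**Cost.** A few more fields and one more summary, with no added procedure, staff or patients. The downsides are slightly longer data capture and the imprecision of visual estimates of blood loss. The protocol does not describe the ward's delivery records, so whether the fields can simply be copied from them needs checking locally.

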2.2. PROBLEM STATEMENT

The pre-induction of labor is an obstetrical procedure that is performed on women to provide a vaginal delivery in those with fetal death. The real benefit of the procedure is to avoid the risk of systemic infection in patients for performing a cesarean section. At present, the treatment indicated to start induction of labor has been established with the use of drugs like prostaglandins. Misoprostol and Dinoprostone have been widely administered during the last decade for inexpensive, easy to administer, effective and safe. However, Misoprostol, like other drug analogs is associated with adverse effects on the mother, especially abdominal pain, nausea, and vaginal bleeding leading to tachycardia that pregnancy is resolved through the abdomen emergency. It is also known that the frequency and intensity of these side effects are increased if the time interval in the pre-induction is prolonged.

At National Institute of Perinatology, the number of fetal deaths over 20 weeks of gestation has increased gradually. During the course of 1998 to 2006, mortality has increased from 95 cases to 211 in the period, with a fetal mortality rate of 38.6 per 1000 births for 2006. The procedures are often used to address labour in women with fetal death, to mention just a few examples, such as caesarean section or use of oxytocin without evidence of cervical ripening can contribute to increased maternal morbidity. In medical practice, using isosorbide dinitrate gel solution prior to induction of cervical dilation might reduce damage, economic cost of surgical procedures and risks to the health of the mother.

2.3. BIBLIOGRAPHIC HISTORY.

**2.3.1 The effect of nitric oxide donors on cervical ripening**

Endothelial cells produce and release vasoactive agents different regulating vascular smooth muscle tone. One such agent is a labile molecule called endothelium-derived relaxing factor (EDRF)17 and has been identified as nitric oxide (NO). The biochemical evidence shows that the vascular endothelium maintains some production of NO at baseline, but under special conditions NO acts as a potent endogenous vasodilator whose half life is very short. The paramagnetic properties of NO (odd number of electrons) contribute to having affinity for heme group which explains that is not associated with this group in the guanylate cyclase (GC).18 This binding causes a substantial increase in production Guanocín cyclic monophosphate (cGMP) in target endothelial cells occurs vascular.19 The vasorelaxation is produced from modulation of cGMP-dependent protein kinases, phosphorylation/dephosphorylation of myosin light chains and control of ion channels K+/Ca+ calcium homeostasis intracelular.20,21

Nitric oxide donors or organic compounds with ester functional group such as isosorbide dinitrate, glyceryl trinitrate (GTN) and pentaerythritol tetranitrate (PETN) have similar pharmacological properties, and like nitroglycerin are frequently prescribed in treating a variety of cardiac vascular disorders. Organic nitrates are reductively metabolised to release NO, which leads GC activation and catalysis in the conversion of GTP to the second messenger cGMP involved in mediating NO.10 Increased cGMP levels leads to relaxation of smooth muscle metabolism resulting NO.11-13 In addition, organic nitrates may participate in the endogenous pathway of NO production by endothelial cells to maintain tone vascular.14-16 This has led to interest in NO metabolic activity and clinical use of drugs as potential nitrovasodilator inducers of relaxation endocervical.9

**2.3.2 Cervical ripening**

The human cervix is ​​composed of a 10 to 15% of smooth muscle cells, and 85 to 90% of tissue conectivo.22 The vascular endothelium layer has a fine columnar epithelium that lines the channel containing a large amount endocervix branched glands and stroma shows an extracellular matrix, mainly collagen protein type I and III.23,24 addition, type IV collagen is present in smooth muscle cells and vessel walls sanguíneos.25 The collagen fibers provide stiffness that can be quickly replaced by collagenases, although the source and control of these enzymes have not yet been completely entendidas.24 The matrix is ​​composed of water, and protoglicosaminoglicanos glycosaminoglycans, as well as dermatan sulfate, heparan.23 hyaluronic acid and fibronectin Elastin sulfate and are located between the collagen fibers forming a thin layer beneath the epithelium proteins. Cervical ripening is the process that allows the cervix change of structure, designed to be tightly closed to maintain an intrauterine pregnancy, organ support expansion facilitating the passage of the fetus. A decrease in collagen content accompanied by an increase of water and hyaluronic acid allows softening of the uterine neck immediately before and during delivery. Structural changes showing the cervix during labor are defined in two phases: 1) maturation, showing the reorganization of collagen, and 2) expansion. Cervical ripening is the fundamental part of the stage that determines the birth, and occurs regardless of the uterinas.23,26 The internal bore of the cervix where cervical ripening process starts is shown in Figure 1. The cervical dilation involving a inflammatory reaction and the presence of a complex cascade of degradative enzymes accompanying rearrangement of extracellular matrix proteins and glicoproteínas.23,27-29 The hyperplasia and hypertrophy of fibroblasts, and tissue hydration growing in cervical region are anatomical and physiological changes that occur at the end of pregnancy.23

**2.3.3 Physiological aspects during cervical ripening**

Cervical ripening begins before the onset of contractions and labour. Cervical ripening is the result of a series of complex biochemical processes ending with the reorganization and restructuring of the collagen molecules where the cervix thins, softens, relaxes and dilates in response to the onset of uterine contractions. During last step of pregnancy, catabolic enzymes initiating the degradation of collagen and other structural proteins of outlayer matrix.23,24

The production of tumor necrosis factor (TNF-α) and interleukin 1 (IL-1β) induce increased the expression of endothelial adhesion molecules and extravasation of neutrophils into the cervical stroma body. It has also been found that high concentrations of hyaluronic acid correlate with induction of IL-1β and TNF-α.30 An increase in the concentration of IL-1β is associated with the expression of the messengers for interleukin-6 (IL-6) in cervix. IL-6 mRNA expression of interleukin 8 (IL-8) in the decidua of the corium and the presence of IL-1β and IL-8 in the amnion affect the beginning to labour.31,32 The presence of other cells like IL-8 that are located in the human cervix such as stromal origin, granulocyte macrophage can participate during labour.31,33 It should be noted that IL-8 levels of cervical origin correlate with collagenase release (matrix metalloprotease cervical-8) and this enzym which also modulate outlayer matrix proteins. 31, 33-36 Increased synthesis of IL-8 stimulates progesterone (PG) and leukotriene production causing dilation of blood vessels favoring the recruitment of polymorphonuclear cells.30 The presence of activated cells undergoing degranulation always accompanies lysis extracelullar.23 After matrix proteins degranulation by neutrophils proteases are a destabilized collagen fiber network. The action of enzymes on stromal cells is strictly limited on time and it is controlled by the concentration of inhibitory proteins present in tissue.30 Proteases matrix metalloproteinase 8 (MMP-8) seems to correlate with cervical ripening (localized mainly on stroma) unlike tissue matrix metalloproteinases 1 and 3.29,37 The use of exogenous interleukin 8 has been successful to ripen the cervix on some animal species.38,39

Moreover, the PG appears to be involved in controlling the maturation/cervical ripening especially the results obtained in animals and humans using anti-progestagens.40,41 Functional progesterone withdrawal conditions and prepares the start to delivery, ie, a change in the receptor-ligand affinity of PG and decreased concentration of the same in the myometrium and/or cervix. Preliminary results sugest the hypothesis that hormone withdrawal can take place in the human myometrium via changes in expression of co-activators progesterone receptor42 or the path of the differential expression of isoforms.43,44 These results support the idea that the disappearance of progesterone may occur through receptors, thereby facilitating the "feedback" of the hormone on pituitary gland. Other non-hormonal mediators involved in the maturation/cervical ripening include prostaglandins and IL-823,24 and uterotoninas such as oxytocin and endothelin-1 that are independent mediators progesterone. Perhaps protease secretory leukocyte inhibitory (SLPI) that is present in the cervical mucus45 during maturation and which is a powerful inhibitor of neutrophil function with antagonistic action to the action of IL-8.46 In addition, activating factor platelets (PAF) is a pro-inflammatory cytokine which accelerates collagenolysis by pathway of induction of monocyte chemoattractant protein 1 (MCP-1) and on regulating RANTES T lymphocyte activation.47 Finally, several neuropeptides such as substance P, capsaicin, neurokinin A, gene-related peptide, calcitonin and secretoneurina belonging to the substances that can contribute efficiently on cervical ripening.48

